### Recruitment {15}

All patients admitted to the participating centers will be screened for potential recruitment. A daily 24-h report of all patients with musculoskeletal disorders will be extracted from the electronic database. Based on this extract, the written and electronic medical records of potential participants will be screened for eligibility by the study team. Eligible participants will be approached in person in the physical therapy practices. All of the information required for ensuring participant eligibility is obtained as part of routine care.

### Assignment of interventions: allocation

#### Sequence generation {16a}

Participants will be randomized in a 1:1:1 allocation ratio to guided meditation, aromatherapy, or standard care. The allocation sequence will be generated using a computer-based random number generator (www.randomizer.net) by an independent data management team not involved in recruitment or intervention delivery. Block randomization with randomly varying block sizes (e.g., 6 and 9) will be used to ensure balanced group allocation and prevent prediction of future assignments. Randomization will be stratified by study center to account for potential center effect.

#### Concealment mechanism {16b}

The allocation sequence will not be accessible to investigators, care providers, or outcome assessors. After confirmation of eligibility and completion of baseline assessments, study personnel will log into the secure platform to obtain the group assignment. The allocation will be revealed only after participant enrollment, thereby preventing selection bias.

#### Implementation {16c}

The allocation sequence will be created and maintained by the independent data management team at the University Hospital Regensburg. Participants will be enrolled by trained study personnel at each participating center. After obtaining written informed consent and completing baseline assessments, the enrolling investigator or study nurse will access the secure randomization platform and enter the participant’s study ID. The platform will automatically assign the participant to one of the three study arms and generate an electronic allocation record. The study monitor will have read-only access to the randomization log for auditing purposes.

### Assignment of interventions: blinding

#### Who will be blinded {17a}

The care providers and outcome assessors will be blinded using a single-masked procedure.

#### Procedure for unblinding if needed {17b}

No unblinding procedure is planned.

### Data collection and management

#### Plans for assessment and collection of outcomes {18a}

The primary and secondary outcomes will be assessed using validated and reliable instruments at baseline (pre-intervention), immediately after the 4-week intervention, and at follow-up visits 3, 6, and 12 months post-intervention.

#### Primary outcomes

Pain intensity: Pain intensity will be measured using the NRS, where participants rate their pain on a scale from 0 (no pain) to 10 (worst pain imaginable). The NRS is widely used in clinical settings and has demonstrated good reliability and validity for measuring pain in musculoskeletal conditions [22].

Perceived stress: Stress levels will be evaluated using the Perceived Stress Questionnaire (PSQ). The PSQ is a reliable self-report instrument commonly used in clinical research to assess subjective stress. It has been validated in various populations, including those with chronic pain [23].

Quality of life: Quality of life will be measured using the EQ-5D questionnaire, which assesses five dimensions of health: mobility, self-care, usual activities, pain/discomfort, and anxiety/depression. The EQ-5D is widely used and has been validated across diverse populations, making it a robust tool for assessing health-related quality of life [24].

#### Secondary outcomes

Pain medication consumption: This will be assessed by reviewing patient medical records and self-reported medication usage during follow-up visits. Participants will provide details of their pain medication use throughout the study period, including type, dosage, and frequency.

Biological sample collection: Venous blood samples will be collected at baseline and after completion of the 4-week intervention. Samples will be processed and stored at − 80 °C until batch analysis. Serum cortisol will be measured using immunoassay methods, and inflammatory biomarkers (CRP and IL-6) will be analyzed using standard ELISA techniques in an accredited laboratory.

Data collection process: Data will be collected by trained study nurses and investigators using standardized electronic case report forms (eCRF). To ensure data quality, all assessors will receive training on the use of study instruments and data collection procedures prior to the start of the trial.

Duplicate measurements will be taken for key variables (e.g., pain intensity) to ensure accuracy. Regular audits of the eCRF will be conducted by the study data management team to identify any missing or inconsistent data.

The Data Safety and Monitoring Board (DSMB) will periodically review the data to ensure ongoing trial integrity.

### Plans to promote participant retention and complete follow-up {18b}

The trial management will monitor all patient follow-up and will contact patients who missed a follow-up appointment. Also, the dates for follow-up visits are set at the end of the previous appointment and patients are reminded of the appointment one week before the scheduled appointment by phone or email. A 14-day window, defined as 7 days before and 7 days after the due date, will be available to complete the follow-up visits.

### Data management {19}

For study data collection, a web-based electronic case report form (eCRF) will be set up within an FDA 21 CFR Part 11 and ICH E6(R2) compliant clinical database management system (CDMS). All data management activities will comply with rules according to the EU-GDPR, including pseudonymized data storage.

Each investigator is responsible to review and ensure the accuracy, completeness, and timeliness of the data reported in the patient’s data entered in the eCRF and will provide his/her signature and date of signature on the eCRF pages. During the study, field monitors will review the eCRF entries by remote, and if necessary, by on-site source data verification in order to ensure accuracy, completeness, and plausibility of data entered. In addition, a central statistical monitoring approach will be applied to improve data quality and site performance. Data entered into the study database will be systematically and periodically checked by senior data management staff for completeness, for omissions, and values requiring further clarification using computerized and manual procedures. Any errors or omissions are entered on Data Query Forms, which are forwarded to the study site for resolution. Quality control audits of all key safety and efficacy data in the database are made prior to locking the database. After study completion, all electronic study data will be transferred to an auditable and system-independent accessible standard data format (CDISC) and stored for at least 10 years.

### Confidentiality {27}

Data will be collected pseudonymized and stored on a server at the University Hospital Regensburg with strictly controlled access for ensuring confidentiality. All analysis will be conducted with deidentified data.

### Plans for collection, laboratory evaluation and storage of biological specimens for genetic or molecular analysis in this trial/future use {33}

Blood samples will be collected for measurement of stress and inflammatory biomarkers (serum cortisol, CRP, IL-6). Samples will be stored in pseudonymized form in the institutional biobank for up to 10 years for analyses related to the study objectives.

## Statistical methods

### Statistical methods for primary and secondary outcomes {20a}

#### Primary estimand

The point estimates for both treatment arms will be presented as mean and standard deviation accompanied by the corresponding 97.5% confidence interval and will be compared between the meditation, the aromatherapy intervention and standard of care. To test the null hypothesis H_0_: μ_diff_ = 0 at a two-sided significance level of 0.025, an analysis of covariance (ANCOVA) with the respective component score at month 6 as dependent variable, treatment arm and center as fixed factor, and pain score at baseline, sex, and age as additional covariates will be used. Results will be presented using estimated marginal means of the difference between both groups accompanied by corresponding 97.5% confidence intervals. The study will be considered as successful if at least one component score shows a significant difference between both treatment arms. Two-sided alpha will be set at 0.025 to adjust for multiple testing.

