### Objectives {7}

The objective of this trial is to examine the effect of adjunct psychosomatic therapies on pain perception, stress, and quality of life in patients with (i) lower back pain, (ii) osteoarthritis, (iii) rheumatoid arthritis, and (iv) fibromyalgia.

Specifically, we aim to:Evaluate the reduction in perceived pain using the Numerical Rating Scale (NRS).Assess changes in stress levels using the Perceived Stress Questionnaire (PSQ).Examine improvements in quality of life with the EQ-5D questionnaire.

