#### Primary outcomes

Pain intensity: Assessed using the Numerical Rating Scale (NRS).

Perceived stress: Evaluated using the Perceived Stress Questionnaire (PSQ).

Quality of life: Measured using the EQ-5D questionnaire.

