### Methods for additional analyses {20b}

Depending on the results of the primary endpoint, subgroup analyses based on age, sex, and diagnosis will be performed.

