Nevertheless, several limitations should be acknowledged. Blinding of participants to behavioral interventions is not feasible and may introduce expectancy effects. Adherence to home-based interventions may vary between participants despite strategies to support compliance. Additionally, the heterogeneous musculoskeletal patient population may increase variability in treatment response, although this reflects real-world clinical practice and enhances generalizability.

In summary, this trial is poised to provide valuable insights into the role of psychosomatic therapies as adjunct treatments for musculoskeletal disorders. By addressing both the psychological and physical dimensions of pain, the study has the potential to influence future clinical practice, promoting a more comprehensive and patient-centered approach to managing chronic musculoskeletal pain. The findings could also open the door for further research on the integration of complementary therapies into mainstream medical and physiotherapeutic treatments, ultimately improving patient outcomes and quality of life.

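### The single ANCOVA adjusts month-6 stress and quality of life for baseline pain and not for their own baselines, which gives up precision on two of the three primary outcomes

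*Protocol article*

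**What the plan says.** Outcomes {12} in the protocol article names three primary outcomes: pain on the NRS, stress on the PSQ and quality of life on the EQ-5D.

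The Primary estimand section under {20a} gives one ANCOVA for all of them, "with the respective component score at month 6 as dependent variable". Arm and centre are fixed factors. Of the remaining terms it says "pain score at baseline, sex, and age as additional covariates will be used". Pain is thus the only baseline outcome score in the model, whichever outcome is analysed. The same section counts the trial a success if at least one component score differs significantly, at two-sided 0.025.

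Outcomes {12} and {18a} have every primary outcome measured at baseline. Concealment mechanism {16b} and Implementation {16c} place the baseline assessments before the allocation is obtained.

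Sample size {14} also uses baseline pain as the covariate, but there the calculation is for pain reduction only.

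**The concern.** For a repeated questionnaire score, the earlier value on the same scale is usually the best single predictor of the later one. The model uses it for NRS and not for PSQ or EQ-5D. Baseline pain is the right covariate for the outcome on which the trial was sized, and it appears to have been carried to the other two unchanged.

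PSQ and EQ-5D are two of the three routes to declaring success. With about 30 patients per arm, an avoidable widening of their intervals matters. A chance difference between arms in starting stress or quality of life would also pass largely into the estimate, because baseline pain is only a partial stand-in for those scores.

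This is not detail left to the SAP. The covariate set is stated, and an SAP that follows the protocol would inherit it.

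**Working it through.** **Inputs from the protocol.** Three primary outcomes ({12}); covariates baseline pain, sex and age, factors arm and centre, two-sided alpha 0.025 ({20a}); 30 per group, effect size 0.5 for pain ({14}).

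**Inputs not in the protocol (assumed).** Correlation of the own baseline with the month-6 score, r_own = 0.5 to 0.7. Correlation of baseline pain with month-6 PSQ or EQ-5D, r_pain = 0.1 to 0.4. Correlation between the two baselines, 0.4, needed only for steps 2 and 4.

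**The plan's own figure.** No figure bears on PSQ or EQ-5D. The nearest is 30 per group for pain, with no baseline correlation stated. If 0.5 is read as a standardised mean difference, 80% power at two-sided 0.05 needs 2 × (1.960 + 0.842)² / 0.25 = 62.8 per group before covariate gain (63 rounded up). Thirty per group then requires 1 − r² = 30/62.8 = 0.478, so r of about 0.72. Whether that sizing is sound is a separate matter. On this reading, the trial's size leans on a strong baseline covariate, which the model supplies for pain and not for the other two outcomes.

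**Step 1: residual variance.** With one covariate, the residual variance of the month-6 score is 1 − r² in SD² units. The ratio own baseline to baseline pain is (1 − r_own²)/(1 − r_pain²). Its inverse is the equivalent multiple of patients, and the square root of that inverse is the inflation of the standard error under the plan.

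| r_own | r_pain | Variance ratio | Reduction | Patients | SE, planned/own |
|---|---|---|---|---|---|
| 0.5 | 0.4 | 0.75/0.84 = 0.893 | 11% | 1.12 | 1.06 |
| 0.5 | 0.1 | 0.75/0.99 = 0.758 | 24% | 1.32 | 1.15 |
| 0.6 | 0.3 | 0.64/0.91 = 0.703 | 30% | 1.42 | 1.19 |
| 0.7 | 0.4 | 0.51/0.84 = 0.607 | 39% | 1.65 | 1.28 |
| 0.7 | 0.1 | 0.51/0.99 = 0.515 | 48% | 1.94 | 1.39 |

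If both correlations are 0.5, the ratio is 1 and swapping one covariate for the other gains nothing.

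**Step 2: validity.** A simulation of 4,000 trials with three arms of 30 (r_own 0.6, r_pain 0.3) gave, under no effect, mean estimates near zero for both models and rejection rates of 0.026 (baseline pain) and 0.027 (own baseline) against the nominal 0.025. The empirical standard errors were 0.252 and 0.211, a ratio of 1.19 as in the table.

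**Step 3: power, for illustration only.** The protocol states no target effect for PSQ or EQ-5D. Borrowing 0.5 SD, power is approximately Φ(0.5/√[(1 − r²) × 2/30] − 2.241). Baseline pain with r from 0.1 to 0.4 gives 0.38 to 0.45. Own baseline with r from 0.5 to 0.7 gives 0.50 to 0.68. The simulated central case gave 0.41 and 0.55.

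**Step 4: chance imbalance.** The difference in baseline means between two arms of 30 has SD √(2/30) = 0.258 SD units, so a difference above 0.25 SD has probability 0.33 per comparison. Under the planned model it reaches the estimate through the partial slope (r_own − 0.4 × r_pain)/(1 − 0.4²). This is 0.50 for correlations (0.5, 0.2), 0.57 for (0.6, 0.3) and 0.64 for (0.7, 0.4). A 0.25 SD imbalance therefore moves the estimate by about 0.13 to 0.16 SD. In the simulation the estimate correlated 0.50 with own-baseline imbalance under the planned model and 0.01 with the own baseline in the model.

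**The case against.** The strongest reply is that nothing here is invalid, and that stands. A reader might infer that leaving out the own baseline biases the comparison. It does not: randomisation protects the estimate, and the planned standard error already reflects chance imbalance. Steps 1 and 4 describe one loss seen from two sides and should not be added together.

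The size is also uncertain, and that stands too. EQ-5D has a pain/discomfort dimension ({18a}), so baseline pain may predict it fairly well and the gain there may be small. Nor should the 0.26 SD spread of baseline differences be set against the 0.5 effect size. A raw baseline difference is not the shift in the estimate, and {14} states 0.5 for pain only.

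The objectives speak of change in stress and improvement in quality of life, which might be read as contradicting an analysis of the month-6 score. They do not: in a randomised comparison, the between-arm difference in change and in follow-up score target the same contrast.

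A reader might also count the absence of diagnosis from the model as an error. The protocol does not support that. Randomisation is stratified by centre only ({16a}), and centre is in the model. Diagnosis has a stated use: "subgroup analyses based on age, sex, and diagnosis will be performed", conditional on the primary result. The Discussion's remark that "the heterogeneous musculoskeletal patient population may increase variability in treatment response" concerns differing response, which a main-effect term does not address. If diagnosis explained an assumed 2% to 10% of residual variance, leaving it out would enlarge the standard error by only 1% to 5%. Which variables enter the imputation model is ordinary SAP detail.

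None of this touches the core point: the model fixes a generally weaker covariate for two primary outcomes while the better one is already collected.

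**Conclusion.** The point holds as a loss of precision, not of validity. As written, {20a} adjusts PSQ and EQ-5D for baseline pain and not for their own baselines; NRS is handled correctly. Under the assumed correlations, own-baseline adjustment removes about 11% to 48% of residual variance, equal to about 1.1 to 1.9 times the patients, and the planned standard errors are 6% to 39% larger than they need be. The direction holds whenever a scale's own baseline predicts its month-6 value better than baseline pain does. The amount cannot be fixed from the protocol, and for EQ-5D it could be close to nothing. The change is worth making because it costs almost nothing and affects two of the three routes to success.

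**What to change.** In {20a}, replace the baseline pain score with *the baseline value of the outcome being analysed*: NRS for NRS, PSQ for PSQ, EQ-5D for EQ-5D. Baseline pain may be kept as an additional covariate in the PSQ and EQ-5D models, at one degree of freedom each. Carry the same wording into the SAP and settle it before any outcome data are seen.

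The cost is one phrase in the protocol and SAP. No new data are needed, and a straight swap uses no extra degrees of freedom. Diagnosis may be added as a prespecified covariate if the team wishes (four levels, 3 degrees of freedom), but this point does not require it.

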**Methods:**

This is a three-arm, prospective, randomized controlled trial conducted in Germany. A total of 90 participants aged 18 to 90 with chronic musculoskeletal disorders will be randomized into one of three groups: (1) guided meditation, (2) aromatherapy, or (3) control receiving standard care. The intervention groups will receive either body-scan meditation (23 min, twice weekly) or aromatherapy (5–10 min daily) for one week. The primary outcomes include pain intensity (measured using the Numerical Rating Scale), perceived stress (measured using the Perceived Stress Questionnaire), and quality of life (measured using the EQ-5D). Secondary outcomes will include pain medication consumption. Follow-up assessments will be conducted at 3-, 6-, and 12-month post-intervention. Data will be analyzed using an intention-to-treat approach with ANCOVA for primary endpoints.

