**Discussion:**

This trial will provide valuable insights into the effectiveness of psychosomatic interventions as adjunct therapies for managing chronic pain and stress in musculoskeletal disorders. If successful, these interventions could be implemented as cost-effective and non-invasive strategies to improve quality of life and pain management for patients with musculoskeletal conditions. The findings may also inform future studies on integrative treatment approaches for chronic pain conditions.

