## Introduction

### Background and rationale {6a}

Musculoskeletal disorders (MSDs) are among the most prevalent chronic conditions globally, significantly impacting pain, stress levels, and quality of life [1, 2]. Conditions such as chronic back pain, osteoarthritis, rheumatoid arthritis, and fibromyalgia are common MSDs that frequently lead to persistent discomfort and functional limitations. Despite advances in conventional medical treatments, many patients with these conditions continue to experience considerable pain and reduced quality of life, prompting a search for additional therapeutic options [3, 4].

Integrative therapies, including psychosomatic approaches, have gained attention as potential adjuncts to conventional treatments for managing chronic pain and stress. Psychosomatic therapies often encompass techniques aimed at enhancing the mind-body connection, which may offer benefits beyond those achieved through standard medical care alone. Interventions such as guided meditation and aromatherapy are designed to promote relaxation, reduce stress, and potentially mitigate pain through non-pharmacological means [5].

Guided meditation, for instance, is a practice that involves directing the participant’s attention to various parts of the body, fostering a state of mindful awareness and relaxation. This approach has shown promise in improving pain management and emotional well-being in various patient populations [6, 7]. Similarly, aromatherapy, which utilizes the inhalation of essential oils, is believed to exert calming effects on the nervous system and could serve as a complementary method for pain and stress relief [8, 9].

This study aims to explore the effects of these complementary psychosomatic therapies on pain, stress, and quality of life in patients with musculoskeletal disorders. By conducting a prospective, three-arm, randomized controlled trial, we will evaluate the effectiveness of guided meditation and aromatherapy compared to standard care. This research seeks to determine whether these integrative approaches can provide meaningful benefits to patients suffering from chronic musculoskeletal conditions. Thus, it is hypothesized that providing patients with easy-to-implement methods for self-regulation, stress management, and anxiety reduction will result in a clinically relevant increase in quality of life scores, reduced pain levels, and fewer limitations in performing daily tasks.

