### Sample size {14}

Assumptions: To determine the required sample size, we based our assumptions on previous studies investigating similar psychosomatic interventions in patients with chronic pain conditions. We assume the following for the primary outcome (pain reduction):

Effect size: A medium effect size of 0.5 is expected between the intervention groups and the control group.

Significance level (*α*): A two-sided significance level of 0.05 will be used.

Power (1-*β*): To detect a clinically meaningful difference, we aim for a statistical power of 80% (*β* = 0.2).

Drop-out rate: We anticipate a drop-out rate of 15% during the follow-up period.

Sample Size Calculation:

Using these assumptions, we calculated the required sample size using G*Power software for analysis of covariance (ANCOVA), with baseline pain scores as a covariate:

Minimum required participants per group: 30 participants in each group (guided meditation, aromatherapy, and control) are required to detect a medium effect size with 80% power at a significance level of 0.05.

Total sample size: Accounting for a 15% drop-out rate, the total number of participants to be recruited is 104 participants.

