## Discussion

The introduction of adjunct psychosomatic interventions in the treatment of musculoskeletal disorders represents a significant step toward integrating a more holistic model of care in clinical practice. Musculoskeletal conditions, such as chronic back pain and arthritis, are often treated with a narrow focus on physical symptoms, neglecting the psychological and emotional components that can exacerbate pain and negatively affect quality of life. This trial seeks to explore the potential benefits of integrating guided meditation and aromatherapy into conventional treatment pathways, addressing both physical and psychological factors that contribute to the burden of these disorders.

By adopting a biopsychosocial approach, this trial aligns with growing evidence that chronic pain is influenced by a combination of biological, psychological, and social factors. Such an approach recognizes that interventions targeting stress reduction, relaxation, and mental well-being can have a tangible impact on pain perception and recovery. If successful, the findings from this trial could reshape clinical guidelines by validating the use of psychosomatic therapies as complementary treatments for chronic musculoskeletal pain.

One of the key strengths of this trial is its multidisciplinary framework. By comparing guided meditation, aromatherapy, and standard care, this study offers a direct evaluation of how these complementary interventions might improve patient outcomes beyond what conventional care can achieve. This trial will also provide critical data on the acceptability of these interventions among patients, which is particularly important for treatments that rely on patient engagement and adherence.

However, recruitment and retention remain key challenges in a trial of this nature. While the proposed interventions are non-invasive and have the potential for high patient acceptability, some participants may find it difficult to adhere to the prescribed regimen of regular meditation or aromatherapy. The long-term follow-up period of 12 months further compounds this challenge, as participants might lose motivation or experience competing priorities over time. To address this, the trial incorporates strategies such as frequent follow-up reminders, personalized contact, and offering flexibility in scheduling, all of which are designed to improve retention and minimize attrition.

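### The only success rule lets one undefined component score carry the whole trial, so a stress-only result could count as success although the trial is sized on pain and its pain claims hang on success

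*Protocol article*

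**What the plan says.** **Outcomes.** The abstract names three primary outcomes: "The primary outcomes include pain intensity (measured using the Numerical Rating Scale), perceived stress (measured using the Perceived Stress Questionnaire), and quality of life" (EQ-5D). Outcomes {12} repeats the list, with stress on the same footing as the others: "Evaluated using the Perceived Stress Questionnaire (PSQ"). Neither place ranks them.

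**Sample size {14}.** The assumptions are introduced with "We assume the following for the primary outcome (pain reduction"), in the singular. Stress and quality of life have no sizing assumption.

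**Primary estimand, under Statistical methods {20a}.** An ANCOVA is run on each component score at month 6 at two-sided 0.025. The verdict on the study is then: "The study will be considered as successful if at least one component score shows a significant difference between both treatment arms". The term *component score* is not defined anywhere in the article.

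**Claims tied to success.** The abstract's Discussion says: "If successful, these interventions could be implemented as cost-effective and non-invasive strategies to improve quality of life and pain management". The main Discussion says that, if successful, the findings could reshape guidelines by "validating the use of psychosomatic therapies as complementary treatments for chronic musculoskeletal pain".

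**The concern.** The success rule works at study level and does not depend on which outcome produced the significant test. The claims that follow from success do depend on it, because they are about pain, and in the abstract also about quality of life. Nothing in the article links the two. No sentence requires a pain effect, ranks the outcomes or limits the conclusion to the outcome that was positive.

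If *component score* means the three primary outcomes, a significant PSQ difference beside an unchanged NRS meets the criterion. The trial could then be reported as a successful trial of adjuncts for chronic musculoskeletal pain, although the outcome it was sized on showed nothing. Splitting alpha correctly over all tests would not cure this. It would control how often some outcome is falsely positive, but not which claim a positive outcome supports.

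**Working it through.** **1. What decides the trial, place by place.**

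| Place | Outcome named | Function |
|---|---|---|
| Abstract; Outcomes {12} | NRS, PSQ, EQ-5D, unranked | list of primary outcomes |
| Sample size {14} | pain, as the single primary outcome | sizing assumption |
| Primary estimand {20a} | any one component score, undefined | the only success rule |
| Abstract (Discussion); Discussion | pain, and in the abstract quality of life | claims made conditional on success |

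The mismatch is in the text and needs no arithmetic. The rest gives a sense of its size.

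**2. The plan's own figure.** The plan gives 30 per group for an effect size of 0.5, two-sided alpha 0.05 and 80% power. For two means without adjustment, n = 2(1.960 + 0.842)² / 0.5² = 62.8, so 63 per group. Thirty follows if the variance is multiplied by 1 − ρ² with a baseline correlation ρ of about 0.73, which the article does not state: 62.8 × (1 − 0.729²) = 29.4, so 30. That is a separate matter. Here 30 per arm is simply taken as the plan's number analysed.

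**3. One stress comparison.** Inputs: 30 per arm and two-sided 0.025 from the plan, and a true effect of 0.5 SD on PSQ (assumed, because the plan gives 0.5 for pain only).
- Standard error of the difference: √(2/30) = 0.258 SD.
- Expected z: 0.5 / 0.258 = 1.94. Critical value: 2.24.
- Power: Φ(1.94 − 2.24) = 0.38.

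**4. The whole rule.** Monte Carlo with three arms of 30, three unit-variance outcomes with assumed correlations of 0.3, 0.5 and 0.7, and pooled t tests of each active arm against control at two-sided 0.025. There is no covariate adjustment. A trial is counted if any test is significant and neither pain test is.

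| True effect | ρ = 0.3 | ρ = 0.5 | ρ = 0.7 |
|---|---|---|---|
| Stress 0.5 SD in both active arms, nothing else | 0.513 | 0.517 | 0.511 |
| Stress 0.5 SD in meditation only, nothing else | 0.391 | 0.374 | 0.372 |

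A second run with 40,000 trials per scenario gave 0.515, 0.509 and 0.510 for the first row and 0.384, 0.377 and 0.368 for the second.

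**5. Cross-check.** A separate calculation with normal rather than t tests gives total success of about 0.58 in the first scenario, with pain significant in about 0.047 of trials, which is chance alone. A significant pain test is itself a success, so success without pain is 0.58 − 0.047 = 0.53. The step from 0.53 to 0.51 comes from using t tests in place of normal ones.

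**The case against.** The case on the other side is substantial, and parts of it stand.

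- **Stress is a deliberate primary outcome.** The abstract, Objectives {7}, Outcomes {12} and the data collection section all name it beside pain and quality of life. An at-least-one rule over several primary outcomes is legitimate if alpha covers all the tests. This stands. The fault is the undifferentiated verdict, not the presence of stress.
- **Sizing on one of several primary outcomes is common and decides nothing.** This stands too. What remains is that Sample size {14} calls pain the primary outcome, in the singular, while success is possible without it.
- **PSQ as a component score is an inference.** Correct, because the term is undefined. If something other than the three primary outcomes is meant, the deciding outcome is fixed even less firmly.
- **The claims are cautious Discussion prose, and negative findings will be published.** Both claims say only what could follow, and each outcome would be reported with its interval. A reader might infer that a stress result automatically triggers a pain claim. The text does not say so. It makes the claims conditional on success, and only one passage defines success.
- **A reader might take the Introduction's hypothesis as a rival, joint criterion.** It predicts a "clinically relevant increase in quality of life scores, reduced pain levels, and fewer limitations in performing daily tasks". This is a background expectation with no test or threshold, and it includes daily limitations, which are not a separately listed outcome. It is not a decision rule. Nor is the sizing assumption, so it would be wrong to say that the sections return opposite verdicts on the same data.
- **The simulation largely restates the power to detect an assumed stress effect.** Fair. It is an illustration. A scenario in which all three outcomes improve would add little, since it would mainly measure low unadjusted power for pain.

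**Conclusion.** The point holds in a limited form. There is one success rule. It rests on an undefined term, and on the most plausible reading it can be met by stress alone. The trial is sized on pain, and the statements conditional on success concern pain.

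If both therapies lowered stress by 0.5 SD and did nothing else, about 51% of trials would be declared successful with no significant pain result. If only one arm had the effect, the figure would be about 37–39%. These figures assume 30 analysed per arm, a stress effect the plan does not state, outcome correlations of 0.3 to 0.7, and unadjusted tests in place of the planned ANCOVA. The textual mismatch depends on none of these assumptions.

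The documents do not support the stronger inference that pain must be the gatekeeper outcome. That is one option for the sponsor.

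**What to change.** 1. In the Primary estimand section, define *component score* as the named primary outcomes (NRS, PSQ, EQ-5D), each at month 6.
2. Replace the study-level at-least-one rule with conclusions specific to outcome and arm: a claim is made only where that outcome's own active-versus-control test is significant after multiplicity adjustment. Three outcomes by two comparisons make six tests. The stated 0.025 equals 0.05/2 and so fits two; an equal Bonferroni split over six would be 0.05/6 = 0.0083.
3. State that any pain conclusion of the kind made in the abstract and the Discussion requires a significant month-6 NRS difference from standard care.
4. Align the singular primary outcome in Sample size {14} with Outcomes {12}, for example by saying that the trial is sized on pain as one of three primary outcomes.

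As an alternative, the sponsor may make month-6 NRS the deciding outcome and test PSQ and EQ-5D after it. This would demote two declared primary outcomes and is not needed to correct the problem.

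Items 1, 3 and 4 and the conclusion rule in item 2 are wording and need no added patients or data. The small cost is that a stress-only result can no longer be called overall trial success. The change should be made before any outcome results by arm are seen.
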